### Viral upper respiratory tract infection

Viral upper respiratory tract infections (URTI) are the most common infectious disease in North America [42]. URTI is the most common reason for emergency department visits and unscheduled outpatient visits in Canada comprising 10% of emergency department visits for children under 10 years of age [2,43]. Preschoolers have the highest incidence of URTI of any age group, occurring 1–2 times per month per child during the winter and higher among children who attend daycare [42,44-49]. Influenza, RSV and adenovirus, which collectively comprise 25% of respiratory infections in children, are the most common viruses that lead to febrile illness, acute otitis media, outpatient visits and hospitalization [44,50]. Roughly 50% of preschoolers with URTI are brought to medical attention resulting in an additional outpatient physician visit every 2 to 3 months during the winter with 1% requiring hospitalization [44,51]. Several groups have estimated the direct and indirect costs of URTI in preschoolers to be between $261 and $276 per URTI with influenza being the most costly virus, contributing $809 per URTI [45,51]. The collective cost of URTI in children under 5 years of age has been estimated to be $1.8 billion annually in the US [52]. Evidence supporting a causal connection between low vitamin D serum levels and URTI comes from multiple sources.

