### Follow-up data collection and data management

Parents of participating children receive a monthly telephone call by a research assistant reminding them to administer the vitamin D supplement daily and record the number of asthma exacerbations, emergency department visits, hospitalizations and missed work days. Parents are also be reminded to collect nasal swabs and complete symptom checklists. In addition, parents are asked to return to their child’s physician’s office in April or May to capture peak respiratory virus season. At the follow-up visit, blood is drawn for 25-hydroxyvitamin D level and a follow-up data collection form completed. The following potential co-interventions are also measured: influenza vaccination, dietary vitamin D intake using a 3 day dietary recall [86], over-the-counter vitamin and mineral supplementation (i.e., calcium containing multivitamins), herbal remedies (i.e., echinacea) and hours per week in daycare (see Additional file 4: Follow-up Data Collection Form). This methodology has been used successfully by our group and others [44,45,98].

To ensure high quality data collection, research assistants are trained in the accurate completion of questionnaires, anthropometric measurement and are registered pediatric phlebotomists as per standard *TARGet Kids!* operating protocol. Weight is measured using a precision digital scale (±0.025% SECA, Hamburg Germany), standing height is measured using a stadiometer (SECA, Hamburg Germany), and skin pigmentation is measured using a narrow-band reflectometer (Dermaspectrometer, Cortex Technology) [108-111]. Questionnaires and URTI symptom checklists have been pilot tested to ensure understandability and reduce incomplete responses [101]. Collected data is electronically entered on a daily basis by research assistants at each site into the study’s central database via a secure web-based data portal.

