### Economic analysis

A cost-effectiveness analyses will be conducted using data from this trial. A societal perspective will be employed to calculate both direct health service utilization costs as well as indirect costs to families of an URTI. The time horizon of the analysis will be limited to the follow-up of this trial in order to leverage direct data. Given the short time horizon, discounting of costs and outcomes will not be applied. This analysis will include the cost of ‘high dose’ vitamin D supplementation, physician visits, medications (antimicrobial and over-the-counter), hospital admissions, emergency department visits and laboratory testing abstracted from the child’s medical record and costs associated with lost income from parental work absenteeism and time out of daycare obtained by monthly telephone call using previously described techniques [45,74,115]. Standard, publicly available costing sources will be used to cost resource utilization parameters. Specifically, we will use cost sources such as the Ontario Health Insurance Programs (OHIP), Ontario Case Costing Initiative (OCCI) and standard Ministry of Health (MOH) reimbursements for diagnostic tests. Sex-weighted hourly wage rate will be derived from Statistics Canada Data. The cost-effectiveness analysis will estimate the cost per laboratory-confirmed URTI avoided. The net benefit regression approach will be used to determine each patient’s net benefit from treatment (NB_
*i*
_) based upon the data collected on resource use and lost parental productivity [116]. Graphs will be used to illustrate the incremental net benefit assuming varying willingness to pay. Each estimate of net benefit will be adjusted for potential confounders through regression. In its simplest form, net benefit regression involves fitting the following simple linear regression model: NB_
*i*
_ = β_0_ + β_TX_TX_
*i*
_ + ϵ_
*i*
_ where TX_
*i*
_ is the *i*^th^ person’s treatment indicator (TX_
*i*
_ = 1 for new treatment and 0 for usual care) and ϵ_
*i*
_ is a stochastic error term [117]. Parametric confidence intervals for incremental net benefit will be compared to results of non-parametric bootstrapping to characterize statistical uncertainty in the economic analysis.

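### The stated source for over-the-counter medicine costs, the child's medical record, cannot capture them for roughly half or more of URTI episodes, so a small part of the societal saving per URTI avoided is under-counted

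*Protocol article*

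**What the plan says.** The Economic analysis section of the protocol article sets the perspective: "A societal perspective will be employed to calculate both direct health service utilization costs as well as indirect costs to families of an URTI". It then sorts the cost items by source. One list covers the high-dose supplement, physician visits and "medications (antimicrobial and over-the-counter), hospital admissions, emergency department visits and laboratory testing abstracted from the child’s medical record". The other covers "costs associated with lost income from parental work absenteeism and time out of daycare obtained by monthly telephone call". Over-the-counter medicines stand in the first list, and medicines of any kind are absent from the second. The result is to be expressed as cost per laboratory-confirmed URTI avoided and as incremental net benefit.

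Under Follow-up data collection and data management, the monthly call is described as asking parents to "record the number of asthma exacerbations, emergency department visits, hospitalizations and missed work days". The April or May follow-up form records, as possible co-interventions, "over-the-counter vitamin and mineral supplementation (i.e., calcium containing multivitamins), herbal remedies (i.e., echinacea) and hours per week in daycare". Neither description mentions cold or fever medicines bought for a URTI.

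The Background section on viral URTI gives the frequency of illness as "occurring 1–2 times per month per child during the winter". On contact with care it says "Roughly 50% of preschoolers with URTI are brought to medical attention". The same sentence then puts the consequence for clinic use in these terms: "resulting in an additional outpatient physician visit every 2 to 3 months during the winter".

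**The concern.** Over-the-counter products are bought without a prescription and often without a visit. A clinic chart can show them only if the child was seen and someone noted the product. By the protocol's own account, a large share of URTIs are never seen.

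The two sides of the cost-effectiveness ratio would then rest on different sets of episodes. The effect is counted from nasal swabs that parents take at home, so an illness managed entirely at home counts in full. Its over-the-counter cost has no stated route into the data.

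Collecting the data in the same way in both arms does not remove the problem. This cost rises with the number of URTIs, so recording only a fraction of it in each arm also records only that fraction of the difference between arms. What is at stake is the completeness of the societal cost in the secondary economic objective and a modest downward pull on the net benefit of high dose, if high dose works.

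**Working it through.** The plan gives no figure for over-the-counter cost, so there is none to reproduce. The check asks what share of episodes the record could cover, and how much money that involves.

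**Inputs from the protocol**
- Share of preschoolers with URTI who are seen: about 50% (Background, viral URTI).
- Visit interval *m*: one extra outpatient visit every 2 to 3 months (same sentence).
- URTI rate *r*: 1 to 2 per month (same section); the Sample size section plans on 1 per month over 4 months, that is 4 per child.
- Planned effect: one fewer URTI, 4 versus 3 (Sample size).
- Cost per URTI: 261 dollars, the lower of the two values cited (Background, viral URTI).

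**Assumptions not in the protocol**
- Probability *c* that a product is charted when the child is seen: 10%, 25%, 50% or 100%.
- Over-the-counter spending per URTI: 5, 10 or 15 dollars.
- The share seen and the charting probability are the same in both arms, and the share of children seen is read as a share of episodes.

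**Step 1. Share of episodes with no visit.** Using the stated share, unseen = 1 − 0.50 = 50%. Using the visit interval, share seen *s* = 1/(*m* × *r*):

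| *r* per month | *m* months | seen | unseen |
|---|---|---|---|
| 1 | 2 | 1/2 = 50% | 50% |
| 1 | 3 | 1/3 = 33% | 67% |
| 2 | 2 | 1/4 = 25% | 75% |
| 2 | 3 | 1/6 = 17% | 83% |

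At the planning rate of 1 per month, 50% to 67% of episodes have no visit. Over the whole range it is 50% to 83%. At 50%, that is 2 of 4 episodes per child on standard dose and 1.5 of 3 on high dose.

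**Step 2. Share of over-the-counter use that reaches the data.** Captured share = *s* × *c*. With *s* = 50%:
- *c* = 10%: 5%
- *c* = 25%: 12.5%
- *c* = 50%: 25%
- *c* = 100%: 50%

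**Step 3. Effect on the between-arm difference.** Captured difference = (4 − 3) × *s* × *c*, which is 0.05 to 0.5 URTI-equivalents of over-the-counter use against a true difference of 1. Even with perfect charting, half of the over-the-counter saving is missed.

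**Step 4. Money.** If the whole saving on one avoided URTI were lost:
- 5/261 = 1.9%
- 10/261 = 3.8%
- 15/261 = 5.7%

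If half were captured, the loss would be 2.50 to 7.50 dollars, and 2.50/261 = 1.0% to 7.50/261 = 2.9%.

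**The case against.** The strongest reply is that the article is condensed and the instruments are not shown. Parents complete a checklist with each URTI and a follow-up form, both in additional files, and the costing relies on cited techniques. Any of these might record over-the-counter use. The description of the monthly call is plainly a summary: Outcomes and measures attributes further items to it, such as parent-reported URTI, otitis media and pneumonia. Its silence on medicines therefore does not show that the question is never asked. The cost sentence is also loosely built. Its first item is the supplement, which the trial provides and nobody would abstract from a chart, so the closing phrase may not govern every item.

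Much of this stands, and it limits how firmly the point can be put. It does not remove it. The article names this cost and, read naturally, assigns it to the record rather than to the telephone call, so this is a stated source and not a detail left out. If another form does collect the information, the sentence names the wrong source and still needs correcting.

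A reader might infer three further things that the documents do not support:
- **That uncharted use will be entered as zero.** The protocol does not say whether it would be zero, missing, imputed or costed per episode.
- **That the sources for time out of daycare contradict each other.** The Economic analysis section states that source, and a shorter list of call items elsewhere in an article is no contradiction.
- **That the loss is worst where it matters most**, because a supplement mainly averts mild illness or because the amount is large beside the supplement's price. The protocol gives neither the severity of the URTIs averted nor a price.

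**Conclusion.** The point holds in a limited form. On its natural reading, the plan takes over-the-counter medicine costs from a source that can hold no visit-based entry for about half of URTI episodes on the stated share, and for 50% to 83% across the protocol's own rates. No section shown names a parent-reported source instead. If high dose reduces URTIs, the over-the-counter saving per confirmed URTI avoided is under-captured and incremental net benefit is biased slightly downward.

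The upper end of the effect, about 2% to 6% of 261 dollars per URTI, rests on the assumed 5 to 15 dollars and on complete loss; partial charting makes it smaller. The 50% is a background literature figure and not a capture rate measured in this trial. The error works against high dose, concerns one minor component of a secondary economic analysis, and leaves the primary outcome untouched. A correction is worthwhile because it is cheap and because home purchases not asked about at the time are hard to recover later.

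**What to change.** In the Economic analysis section, state that over-the-counter medicines used for a URTI are reported by parents, either on the existing monthly call or on the checklist completed with each URTI. Keep the medical record as the source for antimicrobials, visits, admissions and laboratory tests. Add the item to the description of the chosen instrument under Follow-up data collection and data management. If a form already collects it, it is enough to name that form in the Economic analysis section.

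The cost is one added question on a contact that already takes place, with slightly longer calls and some recall error.

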### Ethical considerations

This study was granted ethics approval by The Hospital for Sick Children Research Ethics Board (REB File No.: 1000025147) on September 14, 2011 and was re-approved by the REB for one year ending in September 2015. This study has been registered as a clinical trial (http://www.clinicaltrials.gov, ID NCT01419262). Written informed consent will be obtained from parents of all child participants prior to any data collection (see Additional file 5: Consent Form). Parents will benefit by the provision of 4–8 months of vitamin D supplementation for their child free of charge. Children may directly benefit via the identification of viral etiology for URTI symptoms and through identification of vitamin D deficiency. The child’s pediatrician will receive viral test results as well as blood results and manage their patient according to national clinical guidelines [5]. While a placebo arm may be ethically justified given the lack of evidence supporting improved health outcomes with supplementation, it is unlikely to be feasible given that current AAP vitamin D guidelines recommend vitamin D supplementation for children older than 1 year and the majority of families in our population are following this recommendation [4,29].

A data safety and monitoring board (DSMB) was established and is composed of a pediatrician, an endocrinologist, an infectious disease expert and a biostatistician and is responsible for monitoring of adverse events. All adverse events will be graded for severity (mild to life threatening) and assessed for relationship to the study intervention. The DSMB (which will be blinded to group allocation) will review safety data between years 1 and 2 and will make decisions regarding unblinding of study groups and premature trial termination. As vitamin D dosages in this study are within the Tolerable Upper Intake Level as recommended by Health Canada for children older than 1 year of age (2500 IU per day for children 1–3 years and 3000 IU/day for children 4–8 years), risk of vitamin D excess is low [70]. In addition, other studies which have used vitamin D doses of up to 50,000 IU per week in children did not show evidence of vitamin D toxicity [118,119]. However, we will monitor for adverse events by ensuring that our participating physicians are aware of signs and symptoms of vitamin D toxicity including nephrolithiasis and hypercalcemia. Additionally, each participant will be assessed for vitamin D toxicity at follow-up through measurement of serum calcium, alkaline phosphatase and parathyroid hormone [6,120,121].

### Knowledge translation

Findings from this research will be disseminated directly to the physician participants and their patients. We will share our results at the annual meeting of all the *TARGet Kids!* practices (physicians, nurses, office staff), research team (investigators, research assistants, students), and policy leaders (representatives from Section of Community Paediatrics, Family and Community Practice, Ontario Medical Association, and parent representatives). Downstream dissemination to primary care physicians will occur through formal and informal venues at local levels, such as City Wide Paediatric Rounds, The Hospital for Sick Children Paediatric Update and those held by local physician groups. The results of this study will be shared with the academic community through peer-review publications and presentations at national and international conferences, locally through hospital rounds and presentations, and through our website http://www.targetkids.ca/. Messages will be relevant to professionals working in the fields of pediatrics, family medicine, endocrinology, infectious disease, nursing, dietetics, and public health. We will also share our findings with colleagues at the Ontario Agency for Health Protection and Promotion, the Centre for Effective Practice, the Maternal Infant Child and Youth Research Network (MICYRN), the Ontario Medical Association, the Canadian Paediatric Society and the American Academy of Pediatrics. Opportunities for media coverage will be sought using an experienced knowledge broker.

## Discussion

There is compelling evidence that young children in North America have vitamin D levels significantly lower than experts recommend. Basic science and epidemiological studies make the case that low wintertime vitamin D levels may be related to two common and costly child health outcomes: wintertime viral URTI and asthma exacerbations. The DO IT Trial is the first randomized controlled trial to investigate vitamin D related respiratory health outcomes in preschoolers. The results of this trial will make an immediate contribution by defining clinical practice standards for vitamin D supplementation for young children and provide an evidence base for national vitamin D guidelines.

The key strengths of this study protocol include a novel and important research question, the outcome of which could affect nearly every young child in Canada, rigorous methodology and an implementation strategy that leverages the efficiency of the only primary care research platform for young children in Canada: *TARGet Kids!*. The *TARGet Kids!* infrastructure and collaborations between child health researchers at the St. Michael’s Hospital, The Hospital for Sick Children and community health care providers make this team unique in Canada and position it ideally to carry out this trial on vitamin D supplementation of Canadian preschoolers and provides opportunity for truly integrated knowledge translation. Furthermore, a solid interdisciplinary team of primary care practitioners and highly qualified methodologists has been assembled with established expertise in preventive child health research, vitamin D deficiency, infectious diseases, laboratory medicine, health economics, clinical epidemiology and clinical trials methodology, analysis and data management to conduct this much-needed research.

Data from this RCT will provide essential evidence regarding wintertime vitamin D supplementation and important health outcomes in Canadian children. Potential downstream economic and health benefits of this trial to Canadian children, the health care system and society include reduced population wide morbidity and associated health care and societal costs. The current paper serves as an important step in the dissemination of the DO IT! Trial by outlining the study background, explaining some of the methodological considerations, and providing a detailed description of methods prior to reporting the results of the analyses.
